**Methods:**

The study was a cluster-randomized controlled trial in 30 clinic sites in two districts in Zimbabwe. Clinics were randomised in a 1:1 allocation ratio to the Child Health Intervention for Development Outcomes (CHIDO) intervention or Ministry of Health standard care. The CHIDO intervention comprises three elements: a group ECS parenting programme, an internal savings and lending scheme (ISALS) and case-management home visits by village health workers. The intervention was aimed at caregiver-child dyads (child aged 0–24 months) where the infant was HIV exposed or infected. The primary outcomes were cognitive development (assessed by the Mullen Scales of Early Learning) and retention of the child in HIV care, at 12 months after enrolment. A comprehensive process evaluation was conducted.

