### Sample size

Based on data collected in our pilot study, the mean Mullen ELC Score was 110.6 (standard deviation [SD] 16.1). The coefficient of variation (k) between clusters was 0.07 but this does not take account of the clustering effect of the group-based intervention so a value for k of 0.15 was used. Using these values, assuming a harmonic mean of 16 dyads enrolled per cluster and a loss to follow-up of 20%, 15 clusters per arm were needed to provide 80% power to detect an effect size (difference in means/SD) of 1.23 for the Mullen ELC Score. The same sample size provides 80% power to detect a risk difference of 20% in retention in care, assuming retention is 65% in the control arm and k = 0.2. Based on these calculations our recruitment target was 528 caregiver-child dyads in total from 30 clinics. We recruited 574 dyads to ensure a harmonic mean of 24 dyads was enrolled from the larger seven clinics and a harmonic mean of 12 dyads was enrolled from the smaller eight clinics. This was done to ensure ECS group sizes were sufficient to include 2 ISALS groups per ECS group.

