### Data analysis

Given the small number of clusters in the trial, cluster-level summary methods will be used. Analysis will be intention-to-treat. Age standardised ELC scores will be calculated from a combination of scores in the four cognitive domains of the Mullen Scales at endline using a HIV negative population in this setting, or a USA reference population if a local reference population cannot be obtained. The mean age-standardised composite score for each cluster will be estimated and the difference in means between arms calculated. The 95% CI for the mean difference will be estimated using a stratified t-test, with variance estimated from the residual mean square from an analysis of variance of cluster-specific means on stratum and trial arm. Analysis will adjust as fixed effects for baseline ELC score, stratum, and the following factors if they are imbalanced between arms at enrolment: age of children and caregivers, HIV status of children, socio-economic status and caregivers’ mental health. For the HIV-specific primary outcomes (proportion of children retained in care at 12 months and proportion with unsuppressed viral load) and for binary secondary outcomes, the unadjusted prevalence ratio will be estimated as the ratio of the geometric mean percentage in the intervention cluster versus the control cluster and compared using logistic regression. The main analysis will be complete case, with multiple imputation as a sensitivity analysis for the two primary outcomes, using variables associated with the outcome and with missingness. Further sensitivity analysis will use individual-level logistic regression and compare the result with the cluster-level methods described above.

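### The test named for the primary retention outcome, logistic regression, does not match its estimator (a ratio of geometric mean cluster percentages) and conflicts with the plan's own cluster-level rule

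*Protocol article*

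**What the plan says.** All of this stands in one paragraph, the Data analysis section of the protocol article.

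- It opens with a general rule: "Given the small number of clusters in the trial, cluster-level summary methods will be used".
- For the ELC score it specifies a full cluster-level method: cluster means, a stratified t-test, and variance from the residual mean square of an ANOVA on stratum and arm.
- For retention, viral load and the binary secondary outcomes, the unadjusted prevalence ratio is "the ratio of the geometric mean percentage in the intervention cluster versus the control cluster and compared using logistic regression". The sentence does not state the level of the regression or how clinic enters it, and it gives no method for the confidence interval.
- It closes: "Further sensitivity analysis will use individual-level logistic regression and compare the result with the cluster-level methods described above".

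The Sample size section bases the retention target on between-clinic variation: "80% power to detect a risk difference of 20% in retention in care, assuming retention is 65% in the control arm and k = 0.2".

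**The concern.** Three things do not fit together.

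1. **Estimate and test.** The ratio of geometric means is the exponential of a difference between arms in the mean of the log cluster percentages. Logistic regression estimates a log odds ratio from pooled counts. Its p-value and interval do not belong to the stated ratio, at whatever level it is fitted.
2. **Test and general rule.** The few-clusters rule calls for inference from the variation between clinic summaries. Logistic regression with no further term takes its variance from the binomial distribution of the children.
3. **Main and sensitivity analysis.** The closing sentence contrasts individual-level logistic regression with cluster-level methods, but for binary outcomes the only test named above it is also logistic regression. An analyst cannot tell how the two should differ.

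At stake is the p-value of one of two primary outcomes and of every binary secondary outcome. Someone following the sentence literally could report chance variation between clinics as an effect. The Trial status section says data analysis is ongoing at submission.

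**Working it through.** **Inputs (protocol article).** From Sample size: control retention 65%, a 20-point difference and k = 0.2; "assuming a harmonic mean of 16 dyads enrolled per cluster and a loss to follow-up of 20"%, so 16 × 0.8 = 12.8 analysed per cluster; "15 clusters per arm were needed to provide 80% power". Recruited: 574 dyads, so 574 × 0.8 / 30 = 15.3 analysed per cluster. Assumptions: two-sided 5% level, and an improvement from 65% to 85%.

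**Step 1. Reproduce the stated power.** The cluster-trial formula is

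c = 1 + (1.96 + 0.84)² × [p0(1−p0)/m + p1(1−p1)/m + k²(p0² + p1²)] / (p0−p1)².

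At m = 12.8 the bracket is 0.2275/12.8 + 0.1275/12.8 + 0.04 × (0.4225 + 0.7225) = 0.0178 + 0.0100 + 0.0458 = 0.0735. This gives c = 15.4, and power of 78.8% with 15 clusters per arm. At m = 16, c = 14.3 and power is 81.9%. The stated 80% is therefore reproduced, and 0.0458/0.0735 = 62% of the planning variance is between clinics. A test that leaves that part out is not the test the trial was sized for.

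**Step 2. Does fitting the regression to clinic counts solve it?** No. With arm and stratum as the only covariates, 30 binomial counts and the individual children give the same likelihood apart from a constant. In one simulated data set the arm coefficient was 0.1619 with standard error 0.1898 either way. A clustering term (random effect, robust variance or overdispersion) is needed, and none is named.

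**Step 3. Type I error if no such term is used.** ICC = k²p/(1−p) = 0.04 × 0.65/0.35 = 0.074. Design effect DE = 1 + (m−1) × ICC. Type I error = 2[1 − Φ(1.96/√DE)].

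| k | m | DE | Type I error |
|---|---|---|---|
| 0.20 | 12.8 | 1.88 | 15.3% |
| 0.20 | 15.3 | 2.06 | 17.2% |
| 0.20 | 16 | 2.11 | 17.8% |
| 0.15 | 15.3 | 1.60 | 12.1% |
| 0.10 | 15.3 | 1.27 | 8.2% |

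Unequal clusters raise this a little. With 6 clinics of 10 and 9 of 19 per arm (12 and 24 less 20%), the size-weighted mean is (6×100 + 9×361)/231 = 16.7. Then DE = 2.16 and the error is 18.3%.

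**Step 4. Simulation** (beta-binomial, k = 0.2, 15 clusters per arm, 6,000 runs per setting).

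| Children per cluster, per arm | Naive logistic | t-test on log proportions |
|---|---|---|
| 13, equal | 16.2% | 4.4% |
| 15, equal | 16.7% | 4.5% |
| 16, equal | 18.6% | 5.2% |
| 6 of 10, 9 of 19 | 18.5% | 4.6% |
| 8 of 10, 7 of 19 | 17.8% | 4.9% |

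The last two rows cover both clinic mixes in the article (six small and nine large per arm under Randomisation process; eight and seven under Sample size). Logistic regression that does allow for clinic gave 4.4–5.8% with a t reference and 6.1–6.9% with a cluster-robust z test.

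**The case against.** A reader might infer that the plan ignores clustering for retention and that the trial's false-positive rate is therefore 18%. The article does not support that. Its first sentence on analysis prescribes cluster-level summaries. Its last sentence attaches the words individual-level only to the sensitivity analysis and sets it against cluster-level methods. As logistic regression applies only to binary outcomes, those methods must include the one for retention. For the same reason a reader should not conclude that the main and sensitivity analyses are meant to be identical; the authors evidently intended two. Nor does the article say that the interval for retention comes from the regression. The 18% needs two conditions: no allowance for clinic, and a true k of 0.2, which is a planning value.

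It can also be said that this is a condensed article, and that standard errors and the handling of clinic belong in a statistical analysis plan that is not shown.

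Most of this stands, and it makes the size conditional. It does not remove the defect. The article does not leave the test open; it names one, and that test does not match the stated estimator on any reading. Nor can the phrase be taken as the first stage of a covariate-adjusted cluster analysis, because the sentence concerns the unadjusted ratio.

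**Conclusion.** The sentence is wrong as written and needs changing, though the evident intention was a cluster-level analysis. The mismatch between odds ratio and geometric-mean ratio holds without any assumption. The inflation is conditional: roughly 15–19% if the regression is run with no allowance for clinic, given 65% retention, k = 0.2, 20% loss and a two-sided 5% level. It falls to about 12% at k = 0.15 and 8% at k = 0.10, and to near 5% if clinic is properly allowed for. These figures describe what a literal reading would permit; they are not an established property of the trial.

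**What to change.** In the Data analysis section, for retention and the other binary outcomes, replace the logistic regression comparison by a t-test on log cluster proportions. Take the variance from the residual mean square of an ANOVA on arm and the same stratum term as for the ELC score, and back-transform the difference and its limits to give the prevalence ratio and 95% CI. The logs matter: a t-test on untransformed proportions compares arithmetic means and would leave the mismatch in place. State a continuity rule for clusters at 0%; it should rarely be needed for retention near 65%, but may be for rarer outcomes.

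Keep logistic regression in two places only: as the first stage of a covariate-adjusted two-stage cluster analysis, and as a sensitivity analysis that allows for clinic with a small-sample correction.

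The cost is one sentence and no new data. The interval becomes wider than a naive one, by about √1.88 = 1.37 to √2.06 = 1.44 times in standard error at k = 0.2. The sample size calculation already allowed for that variation.

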### Data sharing

The trial steering committee (principal investigators and investigators) will consider data sharing applications for quantitative and qualitative data. All applications for data sharing must be made through the principal investigator using a standard Data Sharing Form. The trial steering committee convenes a meeting to consider the application. There will be a good reason for turning down a request. Requests will be considered within 4 weeks of being made, and a decision communicated to the applicant as soon as possible thereafter.

### Process evaluation

The process evaluation integrates quantitative and qualitative data collection tools. In addition, key contextual factors that might affect whether the intervention will work in other settings in Zimbabwe were documented. Project documentation will be reviewed to assess whether activities were conducted as scheduled, to identify any delays or gaps, and to check for standardised comparison across intervention sites. Routine programme data were used to track participation in the intervention, complemented by qualitative research, using semi-structured in-depth interviews (IDIs) with ECS staff, case managers, clinic staff and participating caregivers conducted at 3, 6 and 12 months after the start of the programme. There were 24 CCWs, 15 community based trainers (trainers for the ISALS), 17 ECS facilitators, and 13 nurses involved in implementing the intervention.

The research team also conducted an in-depth process evaluation of the ISALS/ECS and case management programme. The process evaluation included gathering general information on programme implementation processes in intervention communities. Participant groups were randomly observed during ISALS collection / ECS sessions to provide data on programme fidelity. Project staff carry an “events diary” to make note of events that were beyond the control of the project, yet have the potential to influence implementation or outcomes (natural disasters, introduction of other ISALS/ECS services, and change in MOHCC standard of care).

IDIs with caregivers were conducted in the intervention arms at two intervals across the project (mid-implementation and end). Caregivers for the IDIs were purposively selected for specific attributes such as high or low levels of engagement in activities, users and non-users of clinical service. These interviews explored perceptions of the community programme, perceptions of clinical and other available services, and positive and negative experiences of the intervention. Semi-structured interviews, with health care staff at intervention clinics and the implementing stakeholders, were conducted to elicit perceptions of the acceptability of the intervention and their own levels of satisfaction and perspectives on its quality.

### Research ethics and approval

Ethical approval has been granted by the Medical Research Council of Zimbabwe (MRCZ/A/1943), Research Council of Zimbabwe, University College London (6789/002) and London School of Hygiene and Tropical Medicine (9912). The exposed Infant register was utilised within the study. This is not a research tool. The register is part of programme data under the Zimbabwe MOHCC data provision. The data are not publicly available and any requests to use that data are made directly to the Zimbabwe MOHCC services and considered on a case-by-case basis.

### Protocol modification

Any deviation from, or changes of, the protocol will be communicated to relevant partners and funding bodies via email. Changes to the current protocol at the Pan-African Clinical Trials Registry will be updated online.

## Discussion

Several studies have highlighted the effectiveness of implementing comprehensive programmes to improve ECD and nutrition outcomes [16, 35]. Research shows poorer child development outcomes in children exposed to HIV especially in resource poor settings [9, 12]. This trial aims to examine the real world effectiveness of a combined parenting and income-generating programme, with the aim of enhancing child stimulation and utilising skill based learning for economic strengthening of populations in resource-limited settings. Prior to the roll out of the trial, the intervention and research procedures were piloted to assess feasibility and acceptability and to inform the details of the final trial design.

Through the 18 ECS sessions, the ISALS training and the home visits over one year we anticipate positive development in growth and cognitive development. We also anticipate improved parental skills, caregiver-child relationships, reduced stress, improved socio-economic resilience and household food security. This trial will contribute towards understanding the effects of integrating different components of care into a comprehensive programme. It will provide useful insight and understanding in delivery methods of comprehensive services and child development in a resource-limited country.

We have used a cluster randomised design to evaluate this community-based intervention as the intervention was delivered at the level of the health facility and it would not have been practical or desirable to randomise individuals within a facility to different standards of care. The trial will determine whether the comprehensive intervention package has an impact on trial outcomes. The detailed process evaluation will allow us to determine whether the intervention was delivered as intended and will provide insights into the strengths and limitations of the different intervention components. It will, however, not be possible to disentangle the effectiveness of the individual intervention components per se. Nevertheless, findings from this trial will contribute to the literature on the effectiveness of parenting interventions and provide insight on how these interventions could be harnessed into the HIV response to maximise child outcome in resource-limited settings.

### Trial status

At the time of the manuscript submission, recruitment for the trial was completed and process evaluation and data analysis ongoing.

## Abbreviations

ACASI: Audio Computer Assisted Self Interviews
ART: Antiretroviral Therapy
CCW: Case Care Workers
CeSHHAR: Centre for Sexual Health and HIV/AIDS Research
CHIDO: Child Health Intervention for Development Outcomes
ECD: Early Childhood Development
ECS: Early Childhood Stimulation
ELC: Early Learning Composite
IDIs: In-depth Interviews
ISALS: Internal Savings and Lending Scheme
MOHCC: Ministry of Health and Child Care
SD: Standard Deviation
